#### Spence Children’s Anxiety Scale

The Spence Children’s Anxiety Scale is a 44-item measure comprising 6 subscales. The scale was designed to measure the severity of children’s and adolescents’ anxiety symptoms based broadly on DSM-IV criteria for anxiety disorders [69]. Respondents rate the degree to which they experience each symptom on a 4-point frequency scale, ranging from 0 (never) to 3 (always). Only items on the Social Phobia and Generalised Anxiety subscales will be administered in the present study. The scale has demonstrated high internal consistency and satisfactory test-retest reliability [18]. It was also reported to show both convergent [70] and divergent [18] validity.

#### Youth Risk Behavior Survey

The Youth Risk Behavior Survey (YRBS) was designed to assess health risk behaviours among school students in years 9–12. For the purposes of the present study, the YRBS will be abbreviated to three items concerning suicidal thoughts, plans and attempts over the preceding month, for which participants will provide a yes-or-no answer. Endorsement of any of these items will trigger the trial’s participant risk management protocol (see below). Studies have shown that the suicidality items demonstrate both substantial reliability [71] and good convergent and divergent validity in high school samples [72].

#### Depression Stigma Scale

The Depression Stigma Scale (DSS) is an 18-item measure that assesses personal and perceived stigma towards depression. In the present study, only the nine-item personal stigma subscale will be used. These items require participants to rate how strongly they personally agree with a statement about depression (e.g., ‘people with depression are unpredictable’) on a 5-point Likert scale ranging from 0 (strongly disagree) to 4 (strongly agree). The sum of each of the items yields a total stigma score, where higher scores indicate greater stigma. The personal stigma subscale of the DSS has been shown to have moderate internal consistency in an adolescent sample [73, 74].

### Predictor variables

#### Schuster Social Support Scale

The Schuster Social Support Scale is a 15-item measure of social support used to examine an individual’s social relationships with others and the associated impact on their emotional functioning. Each item is rated on a 4-point scale from 0 (not at all) through to 3 (all the time). The scale has demonstrated acceptable reliability coefficients [75]. For the present study, 10 items from 2 subscales which measure support from friends and family will be used.

#### Pearlin Mastery Scale

The Pearlin Mastery Scale is a widely used instrument designed to measure participants’ perceived sense of mastery over life outcomes. Respondents are required to rate how strongly they agree or disagree with a list of seven statements on a scale from 1 (strongly disagree) to 4 (strongly agree). The total scores range from 7 to 28, with higher ratings indicative of a higher level of self-mastery, or control of the forces that affect their lives. The scale has shown good construct and predictive validity (see [76]) and good internal consistency [77].

#### Ruminative Response Scale–short version

The Ruminative Response Scale–short version is a 10-item, self-report questionnaire in which participants reflect upon the causes, meanings and consequences of their negative mood states. Participants are asked to rate how well the statements reflect what they generally do when feeling sad, blue or depressed on a 4-point Likert scale from 1 (almost never) to 4 (almost always). Higher scores indicate a greater degree of rumination about negative feelings and experiences. The short version has been shown to be a reliable measure of rumination that is less confounded by depression than the original version [78]. The scale has good construct validity [79] and convergent and discriminant validity [80]. It also has adequate internal consistency (α = 0.77 and 0.72 for the brooding and reflection subscales, respectively) and test-retest stability [78].

#### Personality Inventory for DSM-5 Brief

The Personality Inventory for DSM-5, Brief Form (PID-5-BF), is a 25-item self-rated personality trait assessment scale developed by the American Psychiatric Association’s Personality Disorders Work Group [81]. It measures the five proposed DSM-5 personality trait domains, including negative affect, detachment, antagonism, disinhibition and psychoticism, with each domain composed of five items. The scale asks respondents to rate how well the item describes themselves generally on a 4-point scale from 0 (very false or often false) to 3 (very true or often true). Overall scores range from 0 to 75, with higher scores indicating greater personality dysfunction. The scale has demonstrated good convergent validity with other widely used personality measures [82]. Further, though originally developed for adults, the PID-5 was also shown to be a reliable tool for measuring personality pathology within adolescent populations, with good reliability reported for personality trait domains and strong construct validity [83].

#### Hopelessness Scale for Children–Brief

The Hopelessness Scale for Children (HPLS)–Brief is a 5-item measure adapted from the HPLS [84]. Participants indicate their agreement with statements by circling ‘true’ or ‘false’, and responses are numerically scored. Higher scores reflect greater hopelessness or negative expectations about the future. Internal reliability and test-retest reliability were both found to be reasonable for the shortened version of the HPLS and comparable to the full 17-item version [85].

#### Interpersonal Needs Questionnaire

The shortened measure of the original 25-item Interpersonal Needs Questionnaire (INQ) contains 15 items designed to assess the extent to which participants feel like a burden on the people in their lives (i.e., perceived burdensomeness) and the extent to which they feel disconnected from others (i.e., thwarted belongingness). Statements are rated using a 7-point Likert scale in terms of how accurately they reflect participants’ recent feelings. After coding, higher scores reflect greater levels of thwarted belongingness and perceived burdensomeness. The scale was evaluated to have good internal consistency [86] and construct validity [87].

#### Acquired Capability for Suicide Scale

The Acquired Capability for Suicide Scale is a five-item self-report questionnaire that aims to measure an individual’s capability to enact lethal self-injury. Questions assess fear of death and the pain associated with dying. Items are rated on a scale from 0 (not at all like me) to 4 (very much like me), where higher scores are thought to be more indicative of one’s capacity for lethal self-injury. The scale has shown good convergent and discriminant validity [86] and high internal consistency in previous studies [88].

#### Insomnia Severity Index

The Insomnia Severity Index is a brief instrument with seven items that assess the nature, severity and impact of insomnia upon the responder. Questions assess both day- and night-time aspects of insomnia over the preceding 2 weeks and the associated interference with normal functioning. Items are rated using a 5-point Likert scale, from 0 (no problem) through to 4 (very severe problem). The scale has previously been shown to have excellent internal consistency [89] and good test-retest reliability, as well as face and content validity [90].

#### Reduced Morningness-Eveningness Questionnaire

The Reduced Morningness-Eveningness Questionnaire (MEQr) is a self-report measure consisting of 5 questions (reduced from the original version containing 19 items) designed to explore participants’ sleep and waking rhythms and habits. Known as a circadian questionnaire, the aim of the MEQr is to uncover the individual’s particular biological rhythm. The stability and external validity of the reduced questionnaire have been reported previously [91, 92].

#### Perceived Sensitivity/Perceived Criticism Scale

The Perceived Sensitivity/Perceived Criticism (PS/PC) scale is a very brief measure designed to rapidly assess levels of criticism from relatives as perceived by the participant [44]. The measure is designed to assess how critical the respondent perceives their relative to be and how sensitive the respondent is to this criticism. In the present study, we will ask specifically about how critical students perceive their mother and father to be and how sensitive they are to this criticism. The measure contains two single items, the first for perceived criticism and the second for perceived sensitivity to criticism, which are both rated on a scale from 1 (not at all critical/sensitive) to 10 (very critical/sensitive indeed). The PS/PC scale has been shown to reliably predict outcome for bipolar disorder [93].

### Cortisol and genetics

Cortisol data can be collected via hair strands in classrooms, and the procedure is non-invasive, painless, simple and quick. Saliva samples will also be collected in classrooms using standardised protocols. These data will be used for genetic analysis. Both types of biological data will be collected from students enrolled in the 2016 cohort, pending ethical approval.

### Cost-effectiveness outcomes

#### Trimbos/iMTA questionnaire for Costs associated with Psychiatric Illness

The Trimbos/iMTA questionnaire for Costs associated with Psychiatric Illness questionnaire was designed to assess the costs of psychiatric illness incurred within the health system, as well as the economic burden associated with production loss [94]. In the present study, participants will be asked to recall details about their consultations with health professionals that have occurred over the past 6 months, including clinic visits, appointments, telephone consultations and house calls. The self-report version of the questionnaire consists of 13 items, each requiring a yes-or-no answer and, if relevant, specification of the number of times each particular consultation occurred.

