### Hypotheses

With regard to the primary outcome measure, we predict that, relative to participants in the attention control condition, students who are assigned to the SPARX-R condition will demonstrate lower levels of depressive symptoms immediately following the intervention. We also anticipate that depressive symptoms for SPARX-R participants will be lower than those in the lifeSTYLE group at 6- and 18-month follow-up. For secondary outcomes, we expect that, relative to the lifeSTYLE group, participants in the SPARX-R group will perform significantly better in their HSC and demonstrate reduced anxiety, suicidal ideation and/or behaviour and stigma following the intervention and at follow-up. We anticipate that SPARX-R will have an effect on the parents of students allocated to this group, reducing their own symptom levels at 6 months, relative to parents of students in the attention control group. Finally, we predict that SPARX-R will be more cost-effective than lifeSTYLE, owing to fewer days out of role (e.g., studying, working), better quality of life and less use of health services at 6- and 18-month follow-up.

For those in the SPARX-R group, we predict that a positive response to the prevention program will be associated with the following variables at baseline: absence of family history of depression, high social support, high mastery, low rumination, low neuroticism and/or negative affect, low hopelessness, low thwarted belongingness, low burdensomeness, low sleep disturbance, unimpaired sleep–wake patterns, low expressed emotion, low cortisol levels and lack of genetic vulnerability factors.

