## Methods/Design

### Trial design

This study is a cluster randomised controlled superiority trial with two parallel arms, consisting of an experimental condition and an attention-matched control condition. We will employ an adaptive design, such that accumulating data will be used to decide if or how to modify the study as it continues. To facilitate this design and to stagger recruitment, the trial will take place in two stages across consecutive years, with each stage beginning at the start of the academic calendar (February 2015 and February 2016). The intervention phase will last 5 weeks with a follow-up period of 18 months. Results from the 2015 cohort will be subject to an interim analysis to determine preliminary effects and determine whether any modifications are required in the conduct of the trial in 2016. Feasibility of continuation will also be assessed at this stage in terms of student and teacher acceptability of the intervention and any implementation issues that may arise during the first year of the trial.

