### Procedures

Immediately before the baseline assessment, during an allocated class period, school teachers will provide students with a URL that will take them to the trial registration page. Students will use their unique identification code to register at this page and set up a personal password. Students will also be required to provide a personal email address and mobile telephone number so that they can be contacted during the follow-up period after they have left school.

Students with parental and personal consent will complete questionnaires on three occasions during class time (pre-intervention, post-intervention and 6-month follow-up), as well as an additional 18-month follow-up questionnaire once they have graduated from secondary school. The timing of assessments was designed such that the 6-month follow-up will be conducted just before the trial HSC examination period, one of two major examination periods during the final year of school.

All assessments will be conducted via the online platform. Teachers will direct students to log on to the platform during the first three assessments, and participants will be emailed a link to log on directly from their personal computer on the final assessment occasion. All students will complete their allocated intervention (SPARX-R or lifeSTYLE) over the course of approximately 5–7 weeks in school via the online platform. Schools will timetable the intervention sessions to fit in with their respective schedules, but they will be advised to space sessions out so that students have sufficient time to reflect on the material presented in each module. On each assessment occasion, students who do not complete their assessments during the scheduled class time (owing to absence or other conflicting duties) will be asked to complete the questionnaires in their own time. A reminder email will be sent 1 week after the scheduled assessment, and a final reminder will be sent another week later to any student who still has not completed the scheduled assessment. Trial researchers will monitor completion of assessments and will remain in close contact with participating schools to ensure that school staff encourage assessment and intervention completion by all participating students. Students will no longer be able to access or complete assessments 1 month after their school’s scheduled assessment date.

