### Measures

The administration schedule for each of the assessment measures described below is provided in Table 2.

**Table 2 Tab2:** Assessment administration schedule

Assessment	Construct	Baseline	Post-intervention	6 months	18 months	Other
Primary outcome						
MDI	Depression symptoms	X	X	X	X	
Secondary outcomes						
ATAR	Academic performance					Collected via schools after final examination results are released
SCAS	Anxiety symptoms	X	X	X	X	
YRBS	Suicidal ideation	X	X	X	X	
DSS-P	Personal stigma	X	X	X	X	
Predictor variables						
SSSS	Social support	X				
PMS	Mastery	X	X	X		
RRS	Rumination	X	X	X		
PID-5-BF	Personality traits	X				
HPLS-Brief	Hopelessness	X				
INQ	Belongingness/burdensomeness	X				
ACSS	Capability	X				
ISI	Sleep disturbance	X				
MEQr	Sleep–wake patterns	X				
PS/PC	Expressed emotion	X				
Cost-effectiveness variables						
TiC-P	Service use			X	X	
Questionnaire	Days out of role			X	X	
AQoL	Quality of life			X	X	
Process variables						
Questionnaire	Expectation of success	X				
Intervention data	Adherence					Collected automatically via SPARX-R and lifeSTYLE
Questionnaire	Acceptability, usability		X			
IIAM	Reasons for dropout		X			
Parent outcomes						
PHQ-9	Depression	X		X		
GAD-7	Anxiety	X		X		

*ACSS* Acquired Capability for Suicide Scale; *AQoL* Assessment of Quality of Life; *ATAR* Australian Tertiary Admission Rank; *DSS-P* Depression Stigma Scale–Personal Stigma subscale; *GAD-7* Generalized Anxiety Disorder 7-item scale; *HPLS* Hopelessness Scale for Children; *IIAM* Internet Intervention Adherence Measure; *INQ* Interpersonal Needs Questionnaire; *ISI* Insomnia Severity Index; *MDI* Major Depression Inventory; *MEQr*  Reduced version of the Morningness Eveningness Questionnaire *PS/PC* Perceived Sensitivity/Perceived Criticism scale; *PHQ-9* Patient Health Questionnaire-9; *PID-5-BF* Personality Inventory for DSM-5; Brief Form; *PMS* Pearlin Mastery Scale; *RRS* Ruminative Response Scale; *SCAS* Spence Children’s Anxiety Scale; *SSSS* Schuster Social Support Scale; *TiC-P* Trimbos/iMTA questionnaire for Costs associated with Psychiatric illness; *YRBS* Youth Risk Behavior Survey

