#### Days out of role

This brief questionnaire, administered at 6- and 18-month follow-up, consists of four questions assessing the number of days an individual is unable to attend to (or has some difficulty managing) normal activities (e.g., attending school, university or work) because of mental health problems. Questions were adapted from core items from the World Health Organization Disability Assessment Scale [95] to focus specifically on mental health.

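### Service use is asked at 6 and 18 months with a 6-month recall, so consultations in months 6 to 12, around the examinations, are never recorded

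*Protocol article*

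**What the plan says.** The Hypotheses section of the protocol article predicts that SPARX-R will be more cost-effective than lifeSTYLE. The reasons given are fewer days out of role together with "better quality of life and less use of health services at 6- and 18-month follow-up".

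Three instruments serve this aim, listed in Table 2 (Measures) under "Cost-effectiveness variables":

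- **TiC-P.** The row reads "TiC-P Service use X X"; the two marks stand under 6 and 18 months, and the baseline and post-intervention cells are empty. The section on this questionnaire states a single recall period: "consultations with health professionals that have occurred over the past 6 months". No other period is given for the 18-month wave.
- **Days out of role.** "This brief questionnaire, administered at 6- and 18-month follow-up, consists of four questions". No recall period is stated.
- **AQoL-4D.** The row reads "AQoL Quality of life X X", again at 6 and 18 months only.

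On timing, Trial design says: "The intervention phase will last 5 weeks with a follow-up period of 18 months". Procedures adds that "the 6-month follow-up will be conducted just before the trial HSC examination period" and describes this as one of two major examination periods in the final school year. Trial status dates the first cohort's baseline to February 2015 and its 6-month wave to August 2015, with the 18-month wave due in 2016.

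**The concern.** The waves at which service use is asked are 12 months apart, but the second looks back only 6 months. Half of the interval between them is therefore unobserved. The position of that half matters more than its length. The rationale of the trial is prevention ahead of final examinations, and the 6-month wave is deliberately placed before the first of the two examination periods. Service use would be recorded before the stressor and again well after students have left school, but not while the stressor acts.

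If the programme reduces help-seeking around the examinations, the cost comparison cannot show it. If it moves consultations into or out of that period, the comparison can mislead. This cannot be left to an analysis plan, because the schedule and the recall window decide which data exist.

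A lesser point is that none of the three economic measures has a baseline, whereas the MDI and the questionnaire-based secondary outcomes in Table 2 do.

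**Working it through.** The protocol states no coverage figure to reproduce, so coverage is counted directly.

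**Inputs.** Waves at t = 6 and t = 18 months (Table 2); recall r = 6 months (TiC-P section); follow-up of 18 months (Trial design); baseline in February 2015 and 6-month wave in August 2015 (Trial status).

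**Coverage.** A wave at month t with recall r covers months t − r to t.

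- 6-month wave: 6 − 6 = 0, so months 0 to 6.
- 18-month wave: 18 − 6 = 12, so months 12 to 18.
- Covered: 6 + 6 = 12 of 18 months.
- Not covered: 18 − 12 = 6 months (months 6 to 12); 6/18 = 33%.

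**Calendar, 2015 cohort.** The windows are about February to August 2015 and February to August 2016. The gap is about August 2015 to February 2016.

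**Where the examinations fall.** The 6-month wave comes just before the trial HSC examinations, so these fall in the gap. The article gives no date for the final examinations. They belong to the 2015 school year, and the next academic year starts in February (Trial design), so they should also lie between August 2015 and February 2016. This step is an inference.

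**Sensitivity of the count.**

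- Origin of time: the gap equals the spacing of the waves less the recall, (18 − 6) − 6 = 6 months. It stays 6 months if time is counted from the end of the intervention, although the Trial status dates support counting from baseline.
- Late completion: Procedures closes each assessment 1 month after its scheduled date. A student who is a month late at 6 months and on time at 18 has a gap of 12 − 7 = 5 months. One who is on time at 6 and a month late at 18 has a gap of 13 − 6 = 7 months. The range is 5 to 7 months.

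**Effect of a longer recall.** With a 12-month recall at 18 months, that wave covers 18 − 12 = 6 to 18. Together with months 0 to 6 this gives 18 of 18 months, a gap of 0.

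**Size of a baseline addition.** TiC-P has 13 items and days out of role has 4. The AQoL-4D has five domains of three items with one domain not collected, so 4 × 3 = 12. The total is 13 + 4 + 12 = 29 items.

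**The case against.** The strongest reply is that the hypothesis is worded as comparisons at 6 and 18 months, and the measures are taken at those waves. A 6-month window is also a defensible compromise, because counts of visits are recalled less accurately over a longer period. Cost-effectiveness is an additional aim, neither the primary outcome nor a key secondary one. These points limit the importance of the gap but do not remove it. A claim of cost-effectiveness over an 18-month follow-up needs costs for that period, or a plain statement of which part is missing.

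Three stronger readings are tempting, and the documents do not support them.

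- *A reader might infer that all economic data miss months 6 to 12.* The gap is shown only for TiC-P consultations. Days out of role has no stated recall period, so its coverage cannot be judged.
- *A reader might infer that the missing AQoL baseline wrecks a calculation of quality-adjusted life years.* The article names no such calculation, and how costs and quality of life are combined may be set out in an economic plan that is not shown.
- *A reader might infer that, without baselines, an intervention effect cannot be told apart from initial differences between schools.* Allocation is random among balanced groupings, and the balancing variables are evaluated for the analyses. The missing baseline costs precision and protection against chance imbalance with about 30 clusters; it does not in itself bias the comparison. Baseline MDI, anxiety, sleep and social support are also available as partial substitutes.

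**Conclusion.** The point holds for service use. As written, TiC-P consultations in months 6 to 12 are never recorded: 6 of 18 months, or one third of follow-up (5 to 7 months for individual students who answer late). The unrecorded period contains the trial HSC examinations and very probably the final ones.

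The conclusion rests on two assumptions. One is that the single stated recall period applies at both waves. The other is that the final examinations fall before the next academic year begins. No cost or utility figure can be attached to the gap from the documents.

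The effect is confined to the economic aim and leaves the primary comparison on the MDI untouched. It should still be corrected, because the remedy is cheap and, once the 18-month wave has passed, no longer available. The absence of economic baselines is a secondary matter of efficiency.

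**What to change.** **Main change.** At the 18-month wave, in both cohorts, ask the TiC-P for the period since the 6-month questionnaire, about 12 months. Name the calendar month of that wave in the question, so that students who missed it have the same reference point. Word the days-out-of-role questions to cover the same period. The cost is a change of wording on the existing online platform, notification of the ethics committees, and more recall error in the 18-month counts.

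**If this is not done.** State in the report that service-use costs cover 12 of 18 months and exclude the examination period.

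**Optional.** Add the TiC-P, days-out-of-role and AQoL-4D items at baseline for the 2016 cohort and use them there as covariates. This is about 29 items on top of a battery that already exceeds 110 by the item counts in the Measures sections, so the added burden is roughly a quarter. It helps one cohort only; the missing 2015 baseline should be reported as a limitation. None of these changes adds an AQoL measurement between months 6 and 18, so quality of life during the examinations would still not be measured.
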